### Assessment of Severity

The intensity of the adverse event will be rated adapting the guidelines, where applicable, set by the U.S. FDA Toxicity Grading Scale for Healthy Adult and Adolescent Volunteers Enrolled in Preventive Vaccine Clinical Trials [23] except for mild diarrhea, which will be defined as 3 loose or liquid stools in a 24 hour period.

| Systemic (General) | Mild (Grade 1)                                    | Moderate (Grade 2)                                | Severe (Grade 3)                                                          | Potentially Life Threatening (Grade 4)     |
|---------------------------|----------------------------------------------------------|----------------------------------------------------------|----------------------------------------------------------------------------------|---------------------------------------------------|
| Nausea/vomiting           | No interference with activity or 1 - 2 episodes/24 hours | Some interference with activity or > 2 episodes/24 hours | Prevents daily activity, requires outpatient IV hydration                        | ER visit or hospitalization for hypotensive shock |
| Diarrhea                  | 3 loose stools or < 400 gms/24 hours                     | 4 - 5 stools or 400 - 800 gms/24 hours                   | 6 or more watery stools or > 800gms/24 hours or requires outpatient IV hydration | ER visit or hospitalization                       |

|                                                                                    |                               |                                                                                          |                                                                           |                             |
|------------------------------------------------------------------------------------|-------------------------------|------------------------------------------------------------------------------------------|---------------------------------------------------------------------------|-----------------------------|
| Headache                                                                           | No interference with activity | Repeated use of non-narcotic pain reliever > 24 hours or some interference with activity | Significant; any use of narcotic pain reliever or prevents daily activity | ER visit or hospitalization |
| Fatigue                                                                            | No interference with activity | Some interference with activity                                                          | Significant; prevents daily activity                                      | ER visit or hospitalization |
| Illness or clinical adverse event (as defined according to applicable regulations) | No interference with activity | Some interference with activity not requiring medical intervention                       | Prevents daily activity and requires medical intervention                 | ER visit or hospitalization |

Changes in the severity of an adverse event should be documented to allow an assessment of the duration of the event at each level of intensity to be performed. Adverse events characterized as intermittent require documentation of onset and duration of each episode.

## 8.2. Reporting of Serious Adverse Events (SAE)

SAEs will be reported promptly to the clinical monitor once the investigator determines that the event meets the protocol definition of a SAE. The SAE form will always be completed as thoroughly as possible with all available details of the event, signed by the investigator (or designee) and countersigned by the Clinical Trial Monitor. The investigator will always provide an assessment of causality at the time of the initial report. If deemed necessary by one or more SAEs, the monitor will have the authority to call a temporary moratorium on vaccination, so that get time to review the side-effect data.

## 8.3. Follow-up

Each subject will be followed up till 21 days of vaccination or till recovered from a serious adverse event if any.

## 9. STATISTICS

### 9.1. Analysis of Demographics

Demographic characteristics of subjects enrolled will be tabulated by group and overall.

#### ***Analysis of Safety***

The number and percentage of subjects (with 95% CI) with at least one adverse event (solicited and/or unsolicited) after vaccination and during the 8 days and 21 days follow up period will be compared between the study groups.

The number and percentage of subjects with at least one Serious Adverse Event, with the frequencies of each type of event will be compared between the study groups.

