**Evaluation Criteria:**

**Safety:** Proportion with adverse diarrheal events, i.e. the adverse events in the vaccine group will be compared with that occurring in the placebo group.

**Immunogenicity:** Seroconversion rate (i.e.  $\geq 4$  fold rise in vibriocidal antibody titre) at 7 days to 9 days after the first dose of vaccine and again on 7th day after the second dose (on day 14).

**Study Period:** Vaccine trial: 6 months

|        | Size | Day 0   | Day 14  |
|--------|------|---------|---------|
| ADULTS | 44   | Vaccine | Vaccine |
|        | 44   | Placebo | Placebo |

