## 4. TRIAL DESIGN

### 4.1. End Points

I. In this trial in adults we will compare the live oral cholera vaccine and placebo recipients for: I occurrence of adverse events to show safety, e.g. diarrhea, vomiting, fever, abdominal pain or cramps, headache, loss of appetite, general ill feeling, rash; and

II. Serum vibriocidal antibody response ( $\geq 4$  fold geometric mean folds rise) to serogroup 01, to show immunogenicity.

**4.2. Trial:** After examination of the safety data in adults (i.e. on first consecutive 40 enrolled) and on receipt of DCGI clearance based on safety data, the trial protocol in children will be developed and submitted to DCGI for clearance. The trial will be randomized double blind and placebo controlled. Randomization ratio will be 1:1 of vaccine and placebo.

Healthy adult men and women (aged 18 to 60 years) will be randomized to receive a single dose of either a live oral cholera vaccine VA1.4 or a placebo dose with the diluents used for constituting the vaccine dose as per manufacturer's instruction. Each agent (vaccine or placebo) will be administered to volunteers on day 0 and observed for a day at the research unit and on 2 more consecutive days with clinic visits with extended stay (9 am to 4 pm). Blood samples (10 ml) will be obtained on day -7 to -4 days (prior to administering the agent) for baseline vibriocidal and laboratory assessment. Primary end points are the occurrence of adverse events and serum vibriocidal response. Solicited adverse events will be noted down on day 0-1-2 and on day 7 or 8. On Day 7, Blood samples (3-5 ml) will be obtained for Vibriocidal assessment. On day 14, a second dose of vaccine or placebo would be administered following the same procedure as on day 0. The code for the volunteers on day 14 will remain same as that on day 0. Solicited symptoms and/or adverse events will be recorded on day 15, 16 and 17.

Follow ups of the subjects for the reactogenicity will be done at the clinic or through home visit by the physicians and the health workers recruited for the project. The subject will drink a buffer solution (bicarbonates 2.5g and ascorbic acid and 1.65g) in 100 ml, 5 minutes prior to drinking the vaccine dose. On day 21 third blood sample (10 ml) will be obtained for vibriocidal and safety assessment.

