#### **4.11. Sample Size**

A 1 –sided 95%confidence interval was used to calculate the sample size since this allowed us to rule out clinically unacceptable high rates of diarrheal adverse event occurring during the 3 days after either dose as well as establish that the vaccine induced adequate seroconversion to V. cholerae O1 Inaba among recipients [11].

Assuming a 10% diarrheal rate among placebo and vaccine recipients alike, to exclude a vaccine-placebo difference in the rate of diarrhea of greater than 20% (upper boundary of the 1-tailed 95% confidence interval) with a power of 0.9, the minimum number of subjects required for each group is 39. For serum vibriocidal responses, assuming a background rate of 5% seroconversion among placebo recipients after one dose and a true vibriocidal response in the vaccine group of 60%, to exclude a vaccine-placebo difference of 30% (lower boundary of the 1-tailed 95% confidence interval) with a power of 0.9, the minimum of subjects required for each group was 40. To adjust for the number of persons expected to drop out of the study, at least 44 persons are therefore required in each group.

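### Section 9 omits the comparison that sized the trial (diarrhoea within 3 days after either dose, against a one-sided 95% bound) and lists any adverse event over 8 and 21 days instead

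*Protocol*

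**What the plan says.** **Sizing (4.11).** The stated aim is to "rule out clinically unacceptable high rates of diarrheal adverse event occurring during the 3 days after either dose". The calculation begins "Assuming a 10% diarrheal rate among placebo and vaccine recipients alike" and is meant "to exclude a vaccine-placebo difference in the rate of diarrhea of greater than 20" percentage points ("upper boundary of the 1-tailed 95% confidence interval) with a power of 0.9, the minimum number of subjects required for each group is 39"). After allowance for dropout the plan is 44 per group.

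**Decision (4.12).** An acceptable level of adverse events, chiefly diarrhoea and vomiting and with a pointer back to 4.11, is required before a field trial.

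**Other statements on diarrhoea.** The synopsis gives the safety criterion as "Proportion with adverse diarrheal events, i.e. the adverse events in the vaccine group", compared with placebo. Section 7.2 accepts an increment over placebo below 10% and says diarrhoeal events will be analysed after completion. Neither gives a window or a method.

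**Endpoint labelled primary (4.2).** The occurrence of adverse events, together with the vibriocidal response. Section 4.1 lists diarrhoea as one example among several.

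**Analysis (section 9, Analysis of Safety).** The number and percentage, with 95% CI, of subjects "with at least one adverse event (solicited and/or unsolicited) after vaccination and during the 8 days and 21 days follow up period" are compared between groups, and so are serious adverse events. Section 9.2 sets a 0.05 level without stating sidedness, and 9.5 expects no deviation from this plan.

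**Collection.** The 4.2 narrative says "Solicited adverse events will be noted down on day 0-1-2 and on day 7 or 8" for dose 1, but names days 15, 16 and 17 after dose 2. The flow chart, 4.2.2 and 4.2.3 cover three days after each dose.

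**The concern.** The number of subjects and the go/no-go rule both rest on one comparison, and the section that fixes the analyses describes another. An analyst who follows section 9 as written would not produce the difference in diarrhoea rates within 3 days after either dose, or its upper bound. The figure produced would pool diarrhoea with headache, fever and intercurrent illness over longer periods.

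This is more than detail left for a statistical analysis plan. Section 9 states a different endpoint and different windows, and 9.5 closes the list. A statistical analysis plan faithful to section 9 would not deliver the 4.11 test. If the 4.11 margin were then applied to the any-event rate, the trial would have neither the power nor the error rate that 4.11 claims.

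**Working it through.** **1. Reproduce the plan's figure.** Inputs from 4.11: 10% in both arms, margin 0.20, one-sided 0.05, power 0.90.

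n = [p_v(1−p_v) + p_p(1−p_p)] × (z₀.₉₅ + z₀.₉₀)² / 0.20² = 0.18 × 2.926² / 0.04 = 38.5, rounded up to 39.

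This matches. The same formula for seroconversion (5% v 60%, bound 30 points, so distance 0.55 − 0.30 = 0.25) gives 0.2875 × 2.926² / 0.0625 = 39.4, rounded up to 40, which also matches. The sample size is therefore right for the comparison in 4.11. The issue is that section 9 does not list that comparison.

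**2. Set the windows side by side.** Doses are on days 0 and 14.

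- 4.11: days 0–3 and days 14–17.
- Section 9, 8 days counted from day 0: misses dose 2. Eight days counted from dose 2 would end on day 22, past the 21-day follow-up in 4.7.
- Section 9, 21 days: covers both doses but adds days 4–13 and 18–21, which is 10 + 4 = 14 days outside the post-dose periods.

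**3. What happens if the 20-point bound is applied to any event.** Assume that a proportion b of subjects has some other event, independent of arm and of diarrhoea. The protocol gives no value for b, so 0 to 50% is shown. With diarrhoea rate d:

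any-event rate = 1 − (1−d)(1−b).

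No excess means d = 10% in both arms. A 20-point excess means 10% on placebo and 30% on vaccine. A trial passes if the difference plus 1.645 × its unpooled standard error is below 0.20. Pass probabilities are exact binomial sums with 44 analysed per arm.

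| b | No excess: rate in both arms | Passes | 20-point excess: placebo v vaccine | Any-event difference (points) | Passes |
|---|---|---|---|---|---|
| 0 (diarrhoea only) | 10% | 92% | 10% v 30% | 20 | 6% |
| 10% | 19% | 78% | 19% v 37% | 18 | 8% |
| 20% | 28% | 67% | 28% v 44% | 16 | 11% |
| 30% | 37% | 63% | 37% v 51% | 14 | 16% |
| 50% | 55% | 63% | 55% v 65% | 10 | 26% |

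The normal approximation behind 4.11 gives nearly the same ends of the range: 93% falling to 60%, and 5% rising to 25%. By that formula, 0.90 power for the composite with no excess would need 66, 87, 100 and 106 per arm at b = 10%, 20%, 30% and 50%.

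**4. Test the independence assumption.** Suppose the vaccine also raises other events from 20% to 30%. The any-event rates are then 1 − 0.9×0.8 = 28% and 1 − 0.7×0.7 = 51%. The difference is 23 points, larger than the diarrhoea excess itself, so dilution is not guaranteed.

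**5. Size of the 4.11 v 7.2 conflict.** If the 10% in 7.2 were applied as a one-sided 95% bound, power at 44 per arm with equal 10% rates would be Φ(0.10/√(0.18/44) − 1.645) = 0.47. The number for 0.90 would be 0.18 × 2.926² / 0.01 = 154.1, rounded up to 155 per arm. Section 7.2 does not say whether 10% applies to the observed difference or to a bound.

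**The case against.** Four points can fairly be made for the plan.

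- **The primary label.** A reader might infer that diarrhoea within 3 days is the primary safety endpoint. The documents do not say so: 4.2 gives that label to the occurrence of adverse events, and the any-event comparison in section 9 fits it. Diarrhoea within 3 days is the endpoint used for sizing and for the decision. This stands.
- **Diarrhoea is not ignored.** A reader might infer that it is never compared. The synopsis and 7.2 both promise it, and methods are commonly left to a statistical analysis plan. This stands against a claim that the endpoint goes unanalysed. It does not answer the mismatch, because neither place gives a window or method and 7.2 brings in a different limit.
- **Loose wording in section 9.** The reference to events after vaccination is undefined and could be read to include a post-dose window. That is possible, but no 3-day period is named and the endpoint is still any event.
- **Weakening is not certain.** The background rates are assumed, and the background section describes the adverse effects of VA1.3 as negligible, which favours the low end of the range. The expected events in 8.1 include nausea, abdominal pain and fever. If the vaccine raises these, the composite may be more sensitive, as step 4 shows. This stands, so the table is an illustration.

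On day 3 after dose 1, a reader might infer from 4.2 that data will be lost. The flow chart, 4.2.2 and 4.2.3 all require that day, so this is a slip in the narrative and data capture is not affected.

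**Conclusion.** The point holds as an inconsistency within the protocol. Section 9 omits the comparison on which 4.11 sized the trial and to which 4.12 ties the field-trial decision, and lists a different endpoint over windows that do not match. The promises in the synopsis and 7.2 do not repair this, and the 10-point and 20-point limits conflict. The 39 and 40 per group are correct for what 4.11 describes.

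If the 20-point bound were carried over to any event at 44 per arm, a vaccine with no excess would pass in about 63% of trials at the high end of the assumed background, compared with 92% on diarrhoea. One with a true 20-point diarrhoea excess would pass in about 26%, compared with 6%. These figures rest on an assumed background of 0 to 50%, on other events being unrelated to arm, and on all 44 per arm being analysed. The mismatch itself rests on none of those assumptions. It should be corrected. It does not show that the trial will reach a wrong safety conclusion.

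**What to change.** 1. Add to section 9, as the safety analysis that informs the decision, the proportion with diarrhoea (by the protocol's definition of loose or liquid stools in 24 hours) within 3 days after either dose, meaning days 0–3 or 14–17. Compare the arms by the one-sided 95% upper bound described in 4.11, and also show the result by dose.
2. Keep any adverse event over 8 and 21 days as a supporting analysis, and state the day from which each window is counted.
3. Reconcile the 20-point limit in 4.11 with the 10-point limit in 7.2, and say whether the limit applies to the bound or to the observed difference. If 10 points is meant as a bound, the sample size must be revisited.
4. Align the 4.2 narrative with the flow chart on day 3 after dose 1.

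Items 1, 2 and 4 cost only protocol wording. The CRF pages for days 0–3 and 14–17 already exist under 4.2.2, so no new data are needed. Item 3 is also wording unless the tighter limit is adopted as a bound. All four should be settled before the codes are broken.

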### ***Analysis of immunogenicity***

Demonstration of at least a fourfold rise in serum anti O1 vibriocidal antibody titer will be the measure of vaccine immunogenicity using microtiter method with modification (Mahalanabis *et al.* 2009). The number and percentage of adults (with 95% CI) who exhibit at least a fourfold rise in serum anti-O1 vibriocidal titer after vaccination will be compared between the study groups.

The geometric mean titre among the vaccine and placebo groups at baseline and at day 7 or 8 and at 21 days will be compared. Geometric mean reciprocal folds rise in titre over 7-8 days and 21 days will also be compared between the vaccine and placebo groups. The proportion with  $\geq 4$  fold rise in titre (95% CI) will be compared using Binomial Exact method. The rate ratios (95% CI) for seroconversion between vaccine and placebo groups will also be calculated for 2x2 tables.

**9.2.** The level of significance for statistical tests will be 0.05.

**9.3.** Consideration for study termination are given under 5.2

**9.4.** Source data Form will be preserved securely locked using standard precautions by the Principal Investigators. Computerized data will have backup copies independently kept by the Principal Investigators and by the DBT. Xerox copies of the source data will also be retained by the Director, NICED securely locked.

**9.5.** We do not anticipate any deviation from the above statistical plan.

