#### **4.2.7 Laboratory procedures**

##### **Serum vibriocidal antibody assay**

The vibriocidal antibody assay is a bactericidal assay requiring the presence of complement-fixing antibody bound specifically to vibrios; this serum antibody response increases after clinical cholera or after vaccination. The serum samples from the volunteer prior to immunization and 7 days after each dose will be tested using vibriocidal antibody assay. An increase of titer by 4-fold or greater between baseline and post-immunization sera will be considered a significant antibody response. The vibriocidal assay using the microtiter technique will be performed in the NICED. As a secondary outcome measure vibriocidal antibody titre will be measured in the sample taken on day 21 to compare with baseline titre and with titre on day 7.

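### The titre comparisons (post-dose GMT and geometric mean fold rise) do not adjust for baseline efficiently, although a pre-dose titre is planned for every subject

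*Protocol*

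**What the plan says.** The analysis of immunogenicity in protocol section 9 names two continuous comparisons. The first is of titres at each visit: "The geometric mean titre among the vaccine and placebo groups at baseline and at day 7 or 8 and at 21 days will be compared". The second is of change from baseline: "Geometric mean reciprocal folds rise in titre over 7-8 days and 21 days will also be compared between the vaccine and placebo groups".

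The declared measure is binary: "Demonstration of at least a fourfold rise in serum anti O1 vibriocidal antibody titer will be the measure of vaccine immunogenicity". Its analysis is also given: the proportion with at least a four-"fold rise in titre (95% CI) will be compared using Binomial Exact method", with rate ratios in addition. The laboratory section (4.2.7) defines response against baseline: "An increase of titer by 4-fold or greater between baseline and post-immunization sera will be considered a significant antibody response".

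Section 4.2 has blood drawn on day -7 to -4 "for baseline vibriocidal and laboratory assessment", and section 4.2.4 plans that draw for all 88 subjects. No baseline-adjusted model of titre is named anywhere. Section 9.5 adds: "We do not anticipate any deviation from the above statistical plan".

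**The concern.** Kolkata is described in section 2.2 as highly endemic for cholera, and section 4.12 links higher titres in endemic populations to inapparent or mild infection. Baseline titres can therefore be expected to vary between volunteers. Section 4.3.1 randomises in permuted blocks without stratifying on baseline titre, so with 44 per arm some chance imbalance in baseline is likely.

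The two planned comparisons treat baseline in opposite ways. Post-dose GMT leaves it out. Fold rise takes off the whole of it, which over-corrects if subjects who start high tend to rise less. Two unadjusted answers are planned per visit; they may disagree, and the protocol does not say which leads. At stake is the precision of the titre comparison and its sensitivity to chance imbalance. Validity is not at stake.

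**Working it through.** **The plan's own figures first.** Section 4.11 uses a one-sided 95% limit ("lower boundary of the 1-tailed 95% confidence interval" for seroconversion) and power 0.9.
- Seroconversion, 5% against 60%, excluding a difference of 30 points: variance sum 0.05×0.95 + 0.60×0.40 = 0.2875. Then n = 0.2875 × (1.645 + 1.282)² / (0.55 − 0.30)² = 39.4, rounded up to 40.
- Diarrhoea, 10% in both arms, margin 20 points: n = 0.18 × (1.645 + 1.282)² / 0.20² = 38.5, rounded up to 39.
- 44 against 40 implies a dropout allowance of 1 − 40/44 = 9.1%.

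Both stated figures reproduce. Both rest on proportions, so nothing below alters N.

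**Precision of the titre comparisons.** Let r be the correlation of baseline and post-dose log titre, and k the post-dose SD divided by the baseline SD. Neither is in the protocol, so both are assumptions. The variance of the arm difference, relative to raw post-dose GMT = 1, is:
- fold rise: (k² + 1 − 2rk)/k², which is 2(1 − r) when k = 1
- ANCOVA: 1 − r²

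| r (k = 1) | Raw GMT | Fold rise | ANCOVA | ANCOVA ÷ fold rise, (1 + r)/2 |
|---|---|---|---|---|
| 0.3 | 1 | 1.4 | 0.91 | 0.65 |
| 0.5 | 1 | 1.0 | 0.75 | 0.75 |
| 0.7 | 1 | 0.6 | 0.51 | 0.85 |

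Simulation with 40 per arm (6000 runs per value of r) gave ANCOVA variances of 0.89, 0.77 and 0.50, in agreement.

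**Unequal SDs.** ANCOVA ÷ fold rise is k²(1 − r²)/(k² + 1 − 2rk).

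| k | r = 0.3 | r = 0.5 | r = 0.7 |
|---|---|---|---|
| 1.5 | 0.87 | 0.96 | 1.00 |
| 2 | 0.96 | 1.00 | 0.93 |

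The slope of post on baseline is rk. When it equals 1 (for example r = 0.5, k = 2), fold rise already makes the right adjustment and ANCOVA gains nothing on it. The gain over raw GMT stays at 1 − r² whatever k is.

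**A responder mixture.** The planning rates of 5% and 60% imply a vaccine arm made up of responders and non-responders, with inflated post-dose variance. One simulation used those rates with 40 per arm and these assumed inputs, in log2 units: baseline SD 1 to 2; responder rise averaging 4 with a minimum of 2; assay noise SD 0.5; responder rise falling by 0, 0.5 or 1 per unit of baseline. ANCOVA variance was 0.46 to 0.88 of raw GMT and 0.95 to 1.01 of fold rise. A second simulation at the same rates, with further assumed inputs, gave 0.27 to 0.89 and 0.89 to 1.02. When the chance of responding was also made to fall with baseline titre, ANCOVA against fold rise was 0.51 to 0.93.

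**Cost.** One degree of freedom: a variance factor of 1 + 1/(N − 4) = 1 + 1/76 = 1.013 at 80 evaluable. ANCOVA then breaks even with raw GMT where (1 − r²) × 1.013 = 1, which is r of about 0.11.

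**The case against.** The strongest reply is that little turns on this. The declared measure, the sample size (4.11) and the acceptance criteria (49% in 4.12, 30% in 7.1) are all proportions of responders. No criterion is set on a GMT ratio. That stands. Section 4.1 does word the immunogenicity endpoint partly in terms of geometric mean fold rise, so titre size is not wholly incidental, but it is neither powered nor given a threshold.

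A second reply is that the protocol names no test or model, so a statistical analysis plan could compare GMTs with baseline adjustment. That is possible, and such a plan would settle the point. Still, the protocol names the quantities to be compared, none of them adjusted, and 9.5 expects no departure from them.

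A third reply is that fold rise already uses the baseline. This is correct. A reader might infer from the GMT comparison that the plan ignores baseline altogether; it does not, since both fold rise and the four-fold responder definition are relative to it. A reader might also take r = 0.5 with equal SDs and conclude that 44 per arm is worth 44/0.75 = 58.7, or about 59 per arm, against either planned comparison. That figure should not be used: it rests on one assumed correlation and one assumed SD ratio, and against fold rise the gain can vanish at the protocol's own responder rates.

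Lastly, the baseline GMT comparison may be meant only as description, as no test is specified for it. Description is useful. A test there could detect only chance differences between randomised arms.

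**Conclusion.** The point holds as a modest improvement in precision for the supporting titre analyses. The planned comparisons are valid under randomisation, and the documents give no ground for calling them biased or for questioning N or the responder-based criteria.

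The size cannot be fixed from the protocol, which gives neither r nor the SD of log titre. Against raw post-dose GMT, ANCOVA variance is 0.91 to 0.51 for assumed r of 0.3 to 0.7, with no gain once r falls to about 0.11. Against fold rise, the result runs from no gain (vaccine-arm variance inflated by a responder mixture) to a substantial one (high-baseline subjects responding less often, 0.51 to 0.93). The case for ANCOVA is that it estimates the slope instead of fixing it at 0 or 1. It therefore comes close to the better of the two planned comparisons without having to know in advance which that is.

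**What to change.** In the analysis of immunogenicity, make the between-arm titre comparison an ANCOVA of log titre on arm and log baseline titre, fitted at day 7 and separately at day 21. Report the back-transformed adjusted GMT ratio with its 95% CI. Keep GMTs (baseline included) and geometric mean fold rises by arm as descriptive summaries, and state that no between-arm test is done at baseline. Leave the four-fold responder analysis and the sample size as they are.

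The change is one of wording. It needs no new sample or visit and costs one degree of freedom, about 1% of variance. If a statistical analysis plan already specifies such a model, the protocol text need only be aligned with it.

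### Section 9 does not prescribe the one-sided bounds on the vaccine-minus-placebo difference that sized the trial, so the stated power of 0.9 does not belong to the analysis written down

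*Protocol*

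**What the plan says.** Protocol section 4.11 opens with the basis of the design: "A 1 –sided 95%confidence interval was used to calculate the sample size". For safety, the starting point is "Assuming a 10% diarrheal rate among placebo and vaccine recipients alike". What has to be ruled out is described there as a "difference in the rate of diarrhea of greater than 20% (upper boundary of the 1-tailed 95% confidence interval". At power 0.9 this gives 39 per group. The event is diarrhoea in the three days after either dose. For immunogenicity, it assumes 5% seroconversion on placebo and 60% on vaccine after one dose, a lower one-sided 95% bound above a 30-point difference and power 0.9, which gives 40 per group. Dropout raises this to 44.

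Section 9 differs. The safety analysis compares the percentage of subjects with at least one adverse event, of any kind, over 8 and 21 days. For immunogenicity, the proportions with a fourfold rise "will be compared using Binomial Exact method. The rate ratios (95% CI) for seroconversion between vaccine and placebo groups will also be calculated". Section 9.2 adds: "The level of significance for statistical tests will be 0.05". Section 9.5 adds: "We do not anticipate any deviation from the above statistical plan".

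Acceptance rules also stand elsewhere. Section 4.12(a) refers to 4.11 for an acceptable level of adverse events, and 4.12(b) requires a vibriocidal response of at least 49%. Section 7.1 accepts a response in at least 30% of vaccinees. Section 7.2 accepts a diarrhoea increment over placebo below 10%.

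**The concern.** The sample size and the analysis plan describe different analyses. Section 4.11 needs a risk difference, a margin and a one-sided bound for two named endpoints. Section 9 has none of the three. It does not single out diarrhoea, and it uses another endpoint and other time windows for safety. This is more than detail left to a later analysis plan: section 9 names methods, an effect measure and a level, and 9.5 expects no departure from them.

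Two things are at stake. The stated power describes an analysis that the plan does not contain. And 4.12(a) makes entry to a field trial depend on a 4.11 criterion that section 9 never evaluates, so the interval method, its sidedness and the margin could be chosen after the results are known.

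**Working it through.** **Inputs (section 4.11).** Diarrhoea 10% in both arms, margin 20 points. Seroconversion 60% against 5%, margin 30 points. One-sided 0.05, power 0.9, 1:1 allocation.

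**1. Reproducing the stated sizes.** With unpooled variance V = p1(1−p1) + p2(1−p2) and distance D between the true difference and the margin, n = V(1.645 + 1.282)² / D². The squared term is 8.564.
- Diarrhoea: V = 0.09 + 0.09 = 0.18 and D = 0.20, so n = 0.18 × 8.564 / 0.04 = 38.5, rounded up to 39.
- Seroconversion: V = 0.24 + 0.0475 = 0.2875 and D = 0.55 − 0.30 = 0.25, so n = 0.2875 × 8.564 / 0.0625 = 39.4, rounded up to 40.

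Both match the protocol, so the analysis that carries the power of 0.9 is a one-sided bound on the risk difference.

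**2. Power if the 95% intervals of section 9 are two-sided and read against the same margins.** Power = Φ(D/√(V/n) − 1.96).
- 40 per arm: Φ(2.981 − 1.96) = 0.846 for diarrhoea; Φ(2.949 − 1.96) = 0.839 for seroconversion.
- 44 per arm: 0.878 and 0.871.
- Power 0.9 would need 48 and 49 per arm (squared term 10.507).

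**3. What different readings do with a diarrhoea excess at the margin.** True rates are 30% and 10%. The results come from full enumeration of the two binomials. Fisher's test is an assumed reading of an unmargined 0.05 comparison; the protocol does not name it.

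| Rule | 40 per arm | 44 per arm |
|---|---|---|
| Two-sided Fisher test not significant | 46.6% | 43.9% |
| 4.11 upper bound (Wald) below 20 points | 5.5% | 5.8% |
| 7.2 rule, observed increment under 10 points | 9.6% | 11.7% |

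**4. Seroconversion, same assumed reading.** Take 2/40 responders on placebo. Fisher's test is significant from 9/40 on vaccine (17.5 points). The Wald lower bound exceeds 30 points only from 20/40 (45 points). With a true difference equal to the margin (35% against 5%, 40 per arm), Fisher's test is significant in 92% of trials and the 4.11 bound is met in about 5%.

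**5. Power of the 4.11 analysis with a Newcombe interval (enumeration).** At 40 evaluable per arm, 0.888 for diarrhoea and 0.861 for seroconversion. At 44, 0.903 and 0.889.

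**The case against.** The best defence is that section 9 should not be read alone. Section 4.11 is headed as a sample size section, and acceptance is set out in 4.12 and section 7. No passage says that a non-significant test will be taken as evidence of safety, or that a significant seroconversion test suffices for a field trial. This stands, and it limits the harm. Under 7.2, read as a point estimate, a 30% against 10% excess is accepted in 10 to 12% of trials, well below the 44 to 47% of the Fisher reading. If the true vaccine response were 30%, the observed rate would reach 49% in under 1% of trials (0.6% at 40 per arm, 0.4% at 44).

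Two further points also stand. The method named for seroconversion is unspecified. The name usually denotes a one-proportion procedure, and a reader might infer that the arms are never compared, but a two-sample exact test may have been meant. And a 0.05 level does not contradict a one-sided 95% bound; 9.2 simply leaves the sidedness open.

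The defence does not close the gap. The rules in 4.12(b), 7.1 and 7.2 are not written as bounds on a difference, and their thresholds differ from 4.11. Section 4.12(a) leads back to 4.11, and section 9 does not carry that analysis out. A two-sample exact test without a margin would not supply it.

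**Conclusion.** The mismatch is real and lies inside the protocol. The power of 0.9 is correct for the 4.11 analysis and does not apply to the analysis in section 9. The size depends on how section 9 is read: about 0.84 to 0.85 at 40 per arm if two-sided 95% intervals are set against the margins. The Fisher figures are conditional on a test that the protocol does not name, and show only how far an unmargined comparison is from the 4.11 question.

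A reader might go further and infer that the primary hypotheses go untested, or that an unsafe vaccine would be passed as safe in nearly half of trials. The documents do not support this. Acceptance rules exist in 4.12 and section 7, and the 4.11 bounds can be computed from the data to be collected. The defect is that this analysis is not prespecified and that the acceptance rules disagree.

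**What to change.** In section 9, add as primary analyses (1) the vaccine-minus-placebo difference in diarrhoea within three days of either dose, with a one-sided 95% upper bound, and (2) the difference in seroconversion after dose 1, with a one-sided 95% lower bound, each judged against its prespecified margin. Name the interval method; a score-type interval such as Newcombe's suits these rates. State in 9.2 that these two analyses are one-sided at 0.05. Keep exact binomial intervals for description within each arm and the rate ratio as descriptive.

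Reconcile 4.11 (20 and 30 points), 4.12(b) (49%), 7.1 (30% response) and 7.2 (10% increment) so that one rule governs each endpoint. Which threshold is right is for the sponsor and investigators to decide.

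If the 4.11 margins are kept, the cost is a few sentences and no extra subjects, with the Newcombe power given above: about 0.89 and 0.86 at 40 evaluable per arm. The choice has consequences. If the 10-point diarrhoea increment of 7.2 were instead required of the one-sided bound, n = 0.18 × 8.564 / 0.01 = 154.2, so 155 per arm, and power at 40 per arm would be about 0.44.
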